### Endpoints

Primary endpoint is a two-stage estimation of diagnostic efficiency of the AI-assisted cytology by using histopathological diagnosis as reference. Secondary endpoints include: (1) comparison of diagnostic accuracies among AI-assisted cytology, endoscopy and pathology; (2) construction and validation of prediction model based on cytological outcomes and risk factors; (3) assessment of cost-effectiveness of AI-assisted cytology as pre-endoscopy detection.

### Statistical analysis

The diagnostic accuracy, sensitivity, specificity, positive predictive value (PPV), negative predictive value (NPV), positive likelihood ratio (PLR), and negative likelihood ratio (NLR) for each test will be calculated with 95% confidence intervals. The baseline participant characteristics will be categorized in percentages for categorical variables and as mean ± SD (Standard Deviation) for continuous variables. The Chi-square test and Mann–Whitney *U* test will be used for analysis of differences. Multivariate logistic regression will be adopted for identifying significant variables. Relevant variables obtained will be included in the multivariable model. The probabilities of diagnosis of esophageal HGIN and early ESCC will be calculated, and an external validation will be performed to evaluate the calibration and discrimination abilities of the model by decision curve analysis. A receiver operating characteristic curve (ROC) analysis will also be applied. Statistical analyses will be performed using SPSS statistical software for Windows, version 22.0 (SPSS Inc., Chicago, IL, USA) and the statistical software package R Version 4.0.5. A *p* value < 0.05 is considered statistically significant.

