### Study design

The project will be prospectively executed in five regions with a high prevalence of ESCC, including Huaian, Taizhou, Yangzhou, Suqian and Yancheng, in Jiangsu Province, China. Participants will be free of charge. Our primary objective is to investigate the efficiency of AI-assisted sponge cytology in population-based screening for esophageal HGIN and early ESCC. Secondary objectives include: (1) to establish the diagnostic threshold (i.e. ASC, LSIL [10]) in such cytological detection; (2) to construct a predicting model identifying individuals for further endoscopy examination by co-analyzing cytological features and relevant risk factors; (3) to analyze cost-effectiveness of this AI-assisted cytology in large-scale screening.

This is a two-stage, 5-year-period project. The flowchart of this study is listed in Fig. 1. The procedures include ESCC-related questionnaire collection, esophageal sponge sampling followed by AI-assisted diagnosis, and endoscopic examination and histopathlogical evaluation. Histopathological results are set as standard of diagnosis of esophageal HGIN and ESCC. In the first stage, population-based esophageal sponge cytology and endoscopic examination will be sequentially performed in four years. Data regarding ESCC-related risks, cytological outcomes, and endoscopic and pathological findings will be collected. Diagnostic efficiency and diagnostic threshold of this AI-assisted cytological diagnosis will be evaluated. By co-analyzing cytological outcomes and relevant risks, a prediction model will be constructed to identify individuals with histopathologically confirmed esophageal HGIN and above lesions. In the second stage, an external individual cohort will be enrolled. The prediction model will be validated, and the diagnostic performance will be assessed. Also, cost-efficiency analysis will be performed in two stages. Our working schedule and relevant results of this study are shown in Table 1.

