**Fig. 1 Fig1:**
[figure not shown]
Flowchart of this study. ESCC: esophageal squmaous cell carcinoma

**Table 1 Tab1:** Working schedule of this study

Time length	Activities	Expected stage outcomes
1^st^ year	• Project announcement, planning and preparation • Course training and project coordination • Participant recruitment • Cytological screening &endoscopy • Data collection and transfer • Scientific visit and supervision	♦ Project initiation ♦ Screening 4,000 participants from each site
2^nd^ year	• Participant recruitment • Cytological screening &endoscopy • Data collection and transfer • Scientific visit and supervision	♦ Screening 8,000 participants from each site
3^rd^ year	• Participant recruitment • Cytological screening &endoscopy • Data collection • Scientific visit and supervision	♦Screening 8,000 participants from each site ♦ Interim report ♦ Preparation of the first publication
4^th^ year	• Participant recruitment • Cytological screening &endoscopy • Data collection • Data verification and analysis • Scientific conference	♦ Screening 4,000 participants from each site ♦ Data analysis assessment of diagnostic efficiency construction of prediction model cost-efficiency analysis
5^th^ year	• Participant recruitment • Cytological screening &endoscopy • Data analysis and archive • Project summary	♦ Screening 2,000 participants from each site ♦ External validation ♦ Publication of results ♦ Dissemination of results to public health agencies

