### Sample size calculation

According to our previous data, a sensitivity of 90.0% was present in AI-assisted esophageal HGIN and above lesions [11]. Sample size will be estimated by using the formula:$$\small {n=Z\alpha^2}P(1-P)/\delta^{2}$$

where *n* = required sample size, *P* = anticipated sensitivity. The confidence level is set as 95% in this study, and Zα = the corresponding standard normal deviate 1.96. And, δ = permissible error, which is set as 0.02. Therefore, 864 individuals with esophageal HGIN and above lesions are needed. Taking the drop rate of 20% into account, this number will be 1,080. Since the prevalence of disease is about 1.2–1.5% [5, 14], about 90,000 potential eligible participants are needed. Given a response rate at about 80%, participant recruitment will be about 112,500 individuals with high risks of ESCC. Therefore, we plan to carry out recruitment in 24,000 residents from each of the five regions in the first stage.

Sample size for validation is also calculated by using the abovementioned formula. The anticipated sensitivity, the confidence level, Zα and permissible error are set as 90%, 95% and 1.96 and 0.06, respectively. Therefore, 96 patients with esophageal HGIN and above lesions are needed. Taking the drop rate and the prevalence into account, about 10,000 participants are needed. Hence, 2,000 new individuals will be recruited from each study site in the second stage for the aim of validation of the predicting model.

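### Decision curve analysis is named as the method for calibration and discrimination; ROC covers discrimination, but calibration has no valid measure, and the stage 2 cohort supports temporal validation only

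*Protocol article*

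**What the plan says.** **Method.** In the protocol article, Statistical analysis has the multivariable logistic model produce probabilities of HGIN and early ESCC, and then says that "an external validation will be performed to evaluate the calibration and discrimination abilities of the model by decision curve analysis". The next sentence adds: "A receiver operating characteristic curve (ROC) analysis will also be applied". It does not say whether that ROC analysis is for the cytology result, the model, or the model in the validation cohort. No calibration plot, intercept, slope, observed/expected ratio or Brier score appears anywhere in the article.

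**Cohort.** Study design states: "In the second stage, an external individual cohort will be enrolled". Sample size calculation says where these people come from: "2,000 new individuals will be recruited from each study site in the second stage for the aim of validation of the predicting model". The development data come from the same places: "we plan to carry out recruitment in 24,000 residents from each of the five regions in the first stage". Table 1 puts the second-stage recruitment in year 5: "Screening 2,000 participants from each site".

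**Role.** Under Endpoints, building and validating the model is a secondary endpoint. Study design gives the model's purpose as picking out those who should go on to endoscopy.

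**The concern.** Calibration asks whether predicted risks match observed frequencies. Discrimination asks whether cases are ranked above non-cases. A decision curve answers a third question: at a given risk threshold, does acting on the model do better than referring everyone or no one? An analyst who follows the sentence literally would present a decision curve as evidence of calibration.

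This matters for a model used through a risk cut-off. At a prevalence of 1.2–1.5%, useful cut-offs are likely to be low absolute risks, and a proportional error in predicted risk changes who falls above the line. A published model with an unquantified calibration error could later misdirect referral, even with a good AUC and a favourable decision curve.

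The word *external* adds to this. A reader may take it as evidence that the model works elsewhere, and Table 1 plans to pass results to public health agencies. A later sample from the development sites cannot show that.

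**Working it through.** **1. The plan's own validation figures.** The inputs for sensitivity, confidence level, Z and permissible error "are set as 90%, 95% and 1.96 and 0.06, respectively".

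- n = Z²P(1−P)/δ² = 1.96² × 0.9 × 0.1 / 0.06² = 96.04, stated as 96.
- With 20% drop-out: 96 / 0.8 = 120.
- At 1.2% prevalence: 120 / 0.012 = 10,000 = 5 × 2,000. At 1.5% it would be 8,000.

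The figures reproduce, and no number is in dispute. The formula sizes the cohort for the precision of a sensitivity.

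**2. What each named method can detect.**

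- ROC/AUC depends only on ranks. Multiplying every predicted odds by a constant keeps the ranks, so the AUC cannot change.
- Net benefit at threshold t is NB(t) = TP/N − (FP/N) × t/(1−t). Miscalibration moves people across t, so NB falls, but the curve does not show by how much the risks are wrong.

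**3. Illustration.** Assumptions not in the documents: prevalence 1.2% (the lower end of the protocol's range), normal linear predictor with SD 1.6, 2 million simulated people, and odds correct, doubled or halved. Net benefit is per 10,000.

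| Predictions | O/E | AUC | NB at 1% | NB at 2% | NB at 5% |
|---|---|---|---|---|---|
| Correct | 1.00 | 0.862 | 72.0 | 53.0 | 28.6 |
| Odds doubled | 0.54 | 0.862 | 67.4 | 45.8 | 19.0 |
| Odds halved | 1.91 | 0.862 | 67.1 | 46.8 | 23.0 |
| Refer all | – | – | 20.3 | −81.6 | −399.9 |
| Refer none | – | – | 0 | 0 | 0 |

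Check of the refer-all row at 2%: 0.012 − 0.988 × 0.02/0.98 = −0.00816, or −81.6 per 10,000.

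Relative loss at 2%: 1 − 45.8/53.0 = 14% (doubled) and 1 − 46.8/53.0 = 12% (halved). At 5%: 1 − 18.95/28.59 = 34% and 1 − 22.97/28.59 = 20%. These losses are visible only beside the correctly calibrated curve, which the trial will not have. Beside the two default strategies, both wrong models look useful at all three thresholds.

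**4. Could the planned cohort measure calibration?** Evaluable cases are 10,000 × 0.8 × 0.012 = 96, or 120 at 1.5%. An approximate 95% interval for O/E is the estimate multiplied or divided by exp(1.96/√events): 1.22 for 96 events and 1.20 for 120. An O/E of 1.91 on 96 events would run from about 1.91/1.22 = 1.57 to 1.91 × 1.22 = 2.33. The data can show an error of this size if someone calculates the ratio.

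**5. Source of the cohort.** Development uses 24,000 people from each of five regions in years 1–4. Validation uses 2,000 new people from each of the same sites in year 5. The people and the period differ; the places do not.

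**The case against.** - **Discrimination is covered.** A reader of the decision-curve sentence alone might infer that discrimination too has no valid method. The next sentence plans a ROC analysis, so that reading fails. What remains is that the ROC analysis should be tied to the model in stage 2.
- **No model is shown to pass.** One might infer that a badly calibrated model would pass validation. The article gives no pass criterion, so only the weaker statement, that miscalibration could go undetected, is supported.
- **The decision curve is not blind.** Net benefit falls under miscalibration, and more so at higher thresholds. In a second illustration (logit risk normal with mean −5.3 and SD 1.5; risks halved or doubled), it goes from 6.2 to 5.4 or 5.3 per 1,000 at a 2% threshold, and the doubled model turns negative (−0.42 per 1,000) at 15%. This stands as a limit on the claim, but both wrong models still beat the default strategies at thresholds from 1% to 10%. The two-fold error is itself an assumption; nothing in the documents predicts drift of that size.
- **No participant is misdirected.** The Discussion says that every participant has both cytology and endoscopy, so the model triages no one in this trial. Any harm would come from later use.
- **The cohort's source is open.** Sample size calculation and Table 1 state it plainly, and nowhere does the article say that stage 2 tests a new region. New people from a later year are an independent sample, so the validation has value. The fault lies in the label and in what may be inferred from it.
- **Calibration detail often sits in an analysis plan.** That is true of omitted detail. Here the article names a method for a purpose that it does not serve, which is an error in the text itself.

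**Conclusion.** The sentence is wrong as written. It gives calibration and discrimination to a method that measures net benefit. ROC rescues discrimination; nothing rescues calibration, so one part of a named secondary endpoint has no valid measure. This conclusion rests on the text and on what the methods estimate, not on the simulation. The simulation only shows that the gap can matter: under its assumptions, roughly two-fold errors in predicted risk leave the AUC unchanged and the decision curve above both default strategies at 1%, 2% and 5%.

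The cohort point is accurate but minor: stage 2 is temporal validation at the development sites and cannot speak to transport to new regions.

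The primary endpoint, recruitment and data collection are unaffected. The text should be corrected before the stage 2 analysis.

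**What to change.** In Statistical analysis, replace the sentence with text to this effect: in the stage 2 cohort, calibration will be assessed by calibration-in-the-large, calibration slope and a smoothed calibration plot; discrimination by the C-statistic with its 95% CI; and clinical usefulness by decision curve analysis. In Study design, Table 1 and Statistical analysis, describe stage 2 as temporal validation at the development sites.

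Optional: leave-one-region-out validation on the stage 1 data, reporting the C-statistic and calibration for each held-out region. That would give about 864/5 = 173 cases per region, but only if the cases are spread evenly; the article gives no regional prevalence.

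Cost: a change of wording and a few lines in R, which the plan already uses. No new data and no change to the sample size are needed. The downside is that *external* becomes *temporal*, a more modest claim.

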### Sample size calculation

According to our previous data, a sensitivity of 90.0% was present in AI-assisted esophageal HGIN and above lesions [11]. Sample size will be estimated by using the formula:$$\small {n=Z\alpha^2}P(1-P)/\delta^{2}$$

where *n* = required sample size, *P* = anticipated sensitivity. The confidence level is set as 95% in this study, and Zα = the corresponding standard normal deviate 1.96. And, δ = permissible error, which is set as 0.02. Therefore, 864 individuals with esophageal HGIN and above lesions are needed. Taking the drop rate of 20% into account, this number will be 1,080. Since the prevalence of disease is about 1.2–1.5% [5, 14], about 90,000 potential eligible participants are needed. Given a response rate at about 80%, participant recruitment will be about 112,500 individuals with high risks of ESCC. Therefore, we plan to carry out recruitment in 24,000 residents from each of the five regions in the first stage.

Sample size for validation is also calculated by using the abovementioned formula. The anticipated sensitivity, the confidence level, Zα and permissible error are set as 90%, 95% and 1.96 and 0.06, respectively. Therefore, 96 patients with esophageal HGIN and above lesions are needed. Taking the drop rate and the prevalence into account, about 10,000 participants are needed. Hence, 2,000 new individuals will be recruited from each study site in the second stage for the aim of validation of the predicting model.

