**Methods:**

The study will be prospectively conducted in five regions with a high prevalence of ESCC. AI-assisted sponge cytology and endoscopic examination will be sequentially performed. Based on our previous data, at least 864 patients with esophageal HGIN and above lesions are needed to achieve enough statistical power. And, a calculated 112,500 individuals with high risks of ESCC will be recruited. In the first stage, each 24,000 participants who meet the inclusion criteria will be recruited on a voluntary basis. Setting pathological results as standard reference, diagnostic threshold and according performance of AI-assisted detection will be evaluated. A prediction model will be constructed by co-analyzing cytological results and relevant risk factors. Then, an external validation cohort will be used for validation of the model efficiency. Also, cost-efficiency analysis will be performed. This study protocol was registered on chineseclinicaltrial.gov (ChiCTR1900028524).

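### Recruitment totals disagree between abstract, Table 1 and sample size section, and stage 2 leaves out the 80% response rate used in stage 1, so its ±6-point precision is not assured

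*Protocol article*

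**What the plan says.** All figures are from the protocol article.

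- **Sample size calculation, stage 1.** The planning sensitivity is 90% ("a sensitivity of 90.0% was present in AI-assisted esophageal HGIN and above lesions"), with Z = 1.96 and a "permissible error, which is set as 0.02". This gives 864 cases, raised to 1,080 for a 20% drop rate and to about 90,000 people for a prevalence of 1.2–1.5%. Then: "Given a response rate at about 80%, participant recruitment will be about 112,500 individuals with high risks of ESCC". The next sentence concludes that "we plan to carry out recruitment in 24,000 residents from each of the five regions in the first stage".
- **Sample size calculation, stage 2.** The same formula with a permissible error of 0.06 gives 96 cases. Then: "Taking the drop rate and the prevalence into account, about 10,000 participants are needed". Recruitment is set at 2,000 new people per site.
- **Abstract, Methods.** It states that "a calculated 112,500 individuals with high risks of ESCC will be recruited", and in the following sentence gives 24,000 each for the first stage.
- **Table 1.** Years 1 to 4 list 4,000, 8,000, 8,000 and 4,000 per site, and year 5 lists 2,000. All are worded as screening, for example "Screening 8,000 participants from each site".

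**The concern.** Two things do not fit together. First, 112,500 over five regions is 22,500 each, not 24,000, and the text moves from one to the other as if it followed. Second, stage 1 is inflated for non-response and stage 2 is not, although both end in a number to be recruited per site.

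Behind both lies an undefined count. In the stage 1 calculation, recruitment is the figure before non-response (90,000 divided by 0.8). In the recruitment procedures, where those who volunteer are recruited, and in Table 1, where the same per-site numbers are screened, it is the figure after non-response.

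The practical question is whether 24,000 and 2,000 are invitation targets or completion targets for a site. The statistical question is whether stage 2 delivers its stated ±6 points. The primary endpoint is a two-stage estimate of diagnostic efficiency, so stage 2 precision bears on it as well as on the validation of the prediction model.

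**Working it through.** **Inputs** (Sample size calculation): P = 0.90, Z = 1.96, δ = 0.02 (stage 1) and 0.06 (stage 2), drop rate 20%, prevalence 1.2–1.5%, response rate 80%, five sites.

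**Reproducing the plan.** The formula is n = Z²P(1−P)/δ².

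- Stage 1: 1.96² × 0.09 / 0.02² = 864.36, taken as 864. Then 864/0.8 = 1,080; 1,080/0.012 = 90,000; 90,000/0.8 = 112,500.
- Stage 2: 1.96² × 0.09 / 0.06² = 96.04, taken as 96. Then 96/0.8 = 120; 120/0.012 = 10,000.

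Every step reproduces, and both chains use the 1.2% end of the prevalence range. The 90,000 and the 112,500 do not conflict with each other, since they stand before and after the response step.

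**Where the chains break.**

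- Stage 1: 112,500/5 = 22,500 per site, but 5 × 24,000 = 120,000. That is 7,500 more, or 6.7%. Adding stage 2 does not reconcile the totals, since 120,000 + 10,000 = 130,000.
- Stage 2: the 10,000 is reached exactly without a response rate. Applying it as in stage 1 would give 10,000/0.8 = 12,500, or 2,500 per site.

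**Evaluable cases and half-width on each reading.** The half-width is 1.96 × √(0.09/cases).

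| Reading | Stage | Prevalence | Cases | Half-width (points) |
|---|---|---|---|---|
| Approached | 1 | 1.2% | 120,000 × 0.8 × 0.8 × 0.012 = 921.6 | 1.94 |
| Approached | 2 | 1.2% | 10,000 × 0.8 × 0.8 × 0.012 = 76.8 | 6.71 |
| Approached | 2 | 1.5% | 10,000 × 0.8 × 0.8 × 0.015 = 96 | 6.00 |
| Screened | 1 | 1.2% | 120,000 × 0.8 × 0.012 = 1,152 | 1.73 |
| Screened | 2 | 1.2% | 10,000 × 0.8 × 0.012 = 96 | 6.00 |

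At the midpoint prevalence of 1.35%, the approached reading of stage 2 gives 10,000 × 0.8 × 0.8 × 0.0135 = 86.4 cases, or ±6.3 points.

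On the screened reading, stage 1 puts 120,000 people against the 90,000 that its sensitivity target needs, which is 30,000 more (33%).

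**The case against.** The best defence is that the per-site numbers count people who take part. The abstract recruits eligible volunteers, the recruitment procedures exclude those who refuse, Table 1 screens 2,000 per site in year 5, and the stage 2 sentence speaks of participants needed. On that reading no response step is due in stage 2, and it yields 96 cases as planned. The 24,000 could also be 22,500 rounded up, and stage 1 serves further aims (threshold comparison, model building, cost-effectiveness) that may justify more than the minimum for sensitivity.

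Much of this stands. It shows that a shortfall in stage 2 is conditional and that stage 1 is never short. It does not remove the inconsistency: the stage 1 calculation uses recruitment for the number before non-response, the rounding is not stated, and rounding would explain neither Table 1's label nor the missing step in stage 2.

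Three stronger readings are tempting, and the article does not support them.

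- *Stage 2 will have 77 cases, not 96.* This requires both the approached reading and 1.2% prevalence. At 1.5% the same 10,000 approached gives 96.
- *Stage 1 subjects 30,000 people to unnecessary endoscopy.* The 20% drop applies to them too. If it is mainly missed endoscopy, the extra endoscopies would be nearer 30,000 × 0.8 = 24,000, and the article does not define the drop. Nor does exceeding the sensitivity target show that the numbers are unneeded for the other aims.
- *Stage 1 should be cut to 18,000 screened per site (90,000/5).* The article does not say which count was intended, so nothing in it calls for a cut.

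**Conclusion.** The stated sample sizes are inconsistent. Stage 1 is derived as 112,500 but planned as 120,000 without explanation, and the response rate enters one stage and not the other.

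The consequence is limited. Stage 1 meets its ±2 points on either reading. Stage 2 meets ±6.0 if per-site numbers count people screened. If they count people approached, its half-width lies between ±6.0 (1.5% prevalence) and ±6.7 (1.2%), at most about 0.7 points worse than stated. These figures assume the plan's own 90% sensitivity, 20% drop rate and 80% response rate.

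Severity is moderate: a stated precision is not assured and the sites' targets are ambiguous, but stage 1 precision is not at risk.

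**What to change.** 1. State once whether the per-site numbers are before or after non-response, and use separate terms for people approached and people screened.
2. Apply the response rate the same way in both stages, and give both counts for each stage.
3. Make the abstract, Table 1 and the sample size section give one total per stage. If 24,000 per site is a deliberate increase over 22,500, say so and why.
4. Keep the planned numbers and restate expected cases and precision. Stage 1 is about 922 cases (±1.9 points) if approached or 1,152 (±1.7) if screened, both at 1.2% prevalence. Stage 2 is 96 cases (±6.0) at 1.2% if screened, or 77 to 96 cases (±6.7 to ±6.0) over the stated prevalence range if approached.

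The cost is an edit to the text and Table 1, and possibly a slightly wider stated precision in stage 2. Only if the numbers mean people approached, and the sponsor wants ±6 points held at 1.2% prevalence, would more people be needed: 12,500 approached instead of 10,000.
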